#### Integration into management systems and operations

When referred Hispanic patients call the transplant center to set up their initial transplant evaluation visit, the schedulers who set up appointments will follow a script. The script will briefly describe the education sessions in the HKTP and the routine English transplant programs, explaining that the HKTP delivers the same medical care as the English program, but is provided in Spanish by bilingual and bicultural transplant clinicians, and addresses Hispanic cultural concerns. At the end of the script, the schedulers will ask Hispanic patients whether they prefer the HKTP or the English clinic. If patients prefer the HKTP clinic, then schedulers will encourage patients to bring friends and family members, including family elders, with them to the HKTP clinic.

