### Study design overview

A prospective effectiveness-implementation hybrid design [70] involving pre-post intervention evaluation with matched controls will be used to implement and evaluate the HKTP. Due to design, matched control sites were pre-specified, and were matched with intervention sites based on city population size, Hispanic proportion of the city population, and kidney transplant and LDKT volumes. Although an ideal study design would be a randomized controlled trial that randomizes patients within each center, it is laden by contamination effects. Randomizing at the center level would require a large number of centers to serve as intervention sites and controls, which is costly. To assess other secular trends, data from matched control centers that do not implement the HKTP will be compared. Control sites were selected in different cities than intervention sites to avoid contamination from local implementation efforts. The first year will focus on implementing the HKTP at BUMC and MC over a 12-month period (Aim 1). Remaining years will focus on evaluating the HKTP on Hispanic LDKTs and on program fidelity in years 2–4½ (Aims 2 and 3).

The hypotheses are that the HKTP will lead to a(n):H_1_ Increase in the ratio of Hispanic to non-Hispanic white LDKTs and in the number of Hispanic LDKTsH_2_ Increase in the number of Hispanic ESRD patients added to the waiting listH_3_ Increase in the number of Hispanic potential donors per potential recipientH_4_ Greater satisfaction of Hispanic ESRD patients with culturally competent care

AIM 1: To implement the HKTP at Two Transplant Centers.

The NU team will first provide BUMC and MC with a preliminary set of protocols comprising the HKTP manual of operations, scripts for clinical coordinator and outreach staff to use, and educational materials describing the structure and content of the education sessions and transcriptions. To train the staff and providers at BUMC and MC, a video-based curriculum will be provided that explains the outreach staff’s communications with dialysis patients, and demonstrates NM’s HKTP Director’s education sessions. NM’s HKTP education session PowerPoint slides will also be provided for sites to use. The set of protocols will help BUMC and MC to determine how to modify their organizations to accommodate the HKTP. Publications that provide evidence to support the HKTP’s increase in Hispanic LDKTs will be provided to foster site ‘buy in’ to implement the HKTP [20, 68].

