### Outcome measures

We will assess the reduction in disparities between self-identified Hispanics and non-Hispanic whites in LDKT rates for adult-to-adult living kidney donation. The effectiveness of the HKTP will be assessed by comparing the outcomes before introducing the HKTP and after the HKTP has been fully implemented. Measures will be collected at intervention and control sites in pre and post periods. For the final outcome measures, de-identified, aggregate center-level data will be collected from the Organ Procurement and Transplant Network/United Network for Organ Sharing (OPTN/UNOS) as publically reported data (Table 2). Data from sites’ medical record review will also be collected. Intermediate outcome measures about each Hispanic and non-Hispanic white potential recipient and potential donor will be collected monthly by research directly from intervention and control sites by medical record review to assess the pathways by which the HKTP potentially increases rates of Hispanic LDKT. We expect that the pre-post change will demonstrate a higher number of potential donors who initiate evaluation and complete more steps in the donor evaluation process.

**Table 2 Tab2:** Final and Intermediate outcome measures: transplant center-reported

Construct	Measure description
Final outcomes	
Ratio of Hispanics to Non-Hispanic Whites Receiving LDKTs	This ratio takes into account growth in transplant center volume while also providing a comparison to non-Hispanic whites, necessary for assessing disparities in LDKT [102]. The ratio provides an index of whether the Hispanic LDKT increase has grown over and above the increase observed at a center overall. By using this ratio, factors related to the center’s infrastructure and capacity to perform additional LDKTs that affect both Hispanics and non-Hispanic whites equally are accounted for. Institutional commitments to LDKT that are associated with higher rates of LDKT, can influence willingness to donate or preferences for LDKT, and affect both populations equally (e.g., paired donation, and desensitization efforts), are accounted for.
Number of Hispanic LDKTs	Change in number of Hispanic LDKTs compared to change in number of non-Hispanic white LDKTs will provide evidence that the increase is not at the expense of white patients.

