Number of Hispanic Patients Added to the Waiting list:	An increase in this number indicates success in overcoming barriers in gaining access (referral) to transplantation and completing the evaluation [103].
Number of Hispanic Potential Donors per Potential Recipient	An increase in this proportion reflects success in encouraging more potential living donors to undergo donor evaluation.
Intermediate Outcomes	
# Patients referred by outreach	The aggregate number of patients who were referred by outreach staff. Referral can be made by self, staff at dialysis centers, nephrologists, primary physicians, or transplant outreach staff.
# Patients scheduled/attending the education session	The aggregate number of patients who were scheduled and attended the HKTP education sessions.
# Patients who completed evaluation	The aggregate number of patients who completed the transplant evaluation process.
# Patients waitlisted	The number of additions to the transplant center’s own waiting list will serve as a proxy for access to the waiting list.
# Days on waiting list, dialysis time	The number of days patients have waited on the waiting list to date.
# Pre-emptive transplants	The number of patients who received a living donor transplant prior to going on dialysis.
# Potential donors at each phase of evaluation	The aggregate number of potential living donors who have completed each phase of the donor evaluation process.
# Days for donor to complete each phase of evaluation	The number of days from start to finish of each phase of living donor evaluation from initiation to clearance for donation to donation.
Potential donor disposition	The donor’s evaluation status as: initiated, completed, ruled out, withdrew, alternate donor found.
Contextual Outcomes	
Patient and potential donor socioeconomic status	Age, gender, race/ethnicity, insurance.
Organ Procurement Organization and transplant center factors	ESRD incidence, and transplant center volume.

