A probabilistic sensitivity analysis will be conducted to ascertain the likelihood that changes in the volume of LDKTs at study sites are indeed attributable to implementation of the HKTP. Rather than assigning a single value to each parameter, we will assign a distribution to all parameters in the model. The ranges will be determined by the average value, the standard deviation, and the shape of the spread of the data. A 1-way sensitivity analysis by varying one parameter at one time will be used to identify secular trend threshold values. We will collect intermediate outcome data at control sites to enable more nuanced pretest-posttest analyses. Sensitivity analyses using published [96, 97] and publically reported LDKT volume data from matched controls will be used to adjust for regional variability. In addition, the two transplant centers implementing the HKTP will be compared to each other. To assess the influence of innovative adaptations on outcomes, qualitative data from routine assessments of the modifications to the HKTP (Aim 2), collected at 14 quarterly time periods post-intervention, will be transformed into quantitative parameters, and will be incorporated into a longitudinal data analysis evaluating trend in outcomes over the post-intervention period accounting for quarterly time-varying adaptations.

We expect an increase in satisfaction scores before and after the education sessions by 10% in post-HKTP based on prior studies [98]. Differences in CAHPS composite scores will then be compared between pre- and post-HKTP by each site using a two-sample t-test. A total of 100 patients per site (50 pre-HKTP, 50 post-HKTP) provides 80% power to detect a difference of 10% (SD = 18%) in mean satisfaction scores before and after education sessions between pre- and post-HKTP groups using a two-sided t-test with a *p* = 0.05 significance level.

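### The education-session intermediate outcome counts only HKTP sessions, so it is zero before the programme and at control centers and cannot support the planned controlled pre-post comparison; the outreach-referral row is ambiguous

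*Protocol article*

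**What the plan says.** Table 2 (Protocol article, Outcome measures) lists the intermediate outcomes. The education row is defined as "The aggregate number of patients who were scheduled and attended the HKTP education sessions". The outreach row is defined as "The aggregate number of patients who were referred by outreach staff", and its next sentence reads "Referral can be made by self, staff at dialysis centers, nephrologists, primary physicians, or transplant outreach staff".

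The same section sets out how the measures are to be used: "Measures will be collected at intervention and control sites in pre and post periods". It adds: "Intermediate outcome measures about each Hispanic and non-Hispanic white potential recipient and potential donor will be collected monthly". The stated purpose is to trace the pathways by which the HKTP might raise Hispanic living donor transplant rates. Aim 3 applies the pre-post evaluation with matched controls to intermediate as well as final outcomes. The Statistical analysis plan section repeats the intention: "We will collect intermediate outcome data at control sites to enable more nuanced pretest-posttest analyses".

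On exposure, the Study design overview says that "data from matched control centers that do not implement the HKTP will be compared". On who attends, the section Integration into management systems and operations says that, after describing both the HKTP and the routine English programme, "the schedulers will ask Hispanic patients whether they prefer the HKTP or the English clinic". Table 1 (component 2) likewise has schedulers offer the HKTP clinic to Hispanic callers.

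**The concern.** An outcome in a controlled pre-post comparison has to be able to take a value in every cell being compared. The education row is tied to a service that exists in one cell only. Any delivery of the programme then shows as an increase over the pre-period and over the controls, whether or not more Hispanic patients receive transplant education. The count measures delivery of the intervention rather than its effect.

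The clinic choice adds substitution. Patients who call for evaluation are asked which clinic they want, so some or all HKTP attendees may be people who would otherwise have attended the routine sessions. The outreach row raises a similar question: a referral through outreach staff may replace one that would have come from a nephrologist.

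These two rows stand at the entry to the pathway that the Discussion plans to map from components to intermediate outcomes to final outcomes. Table 2 has no count of all referrals and none of recipients who start evaluation. Entry into evaluation, which outreach targets directly, is therefore not measured in a form that can be compared across periods and sites.

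**Working it through.** The plan gives no figure for these counts. The check sets each definition against the cells in which it is to be collected.

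**Education row, by period and site**

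| | Before HKTP | After HKTP |
|---|---|---|
| Intervention center | 0 (no HKTP sessions yet) | H |
| Control center | 0 (no HKTP) | 0 (no HKTP) |

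Here H is the number attending HKTP sessions in the post period.

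- Controlled contrast: (H − 0) − (0 − 0) = H. The control center contributes nothing.
- A pre-post ratio has a zero denominator.
- By ethnicity, schedulers offer the clinic to Hispanic patients, so the non-Hispanic white count is expected to be about zero. A Hispanic-to-white ratio would be undefined or unstable.

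**Substitution**

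Let R0 and R1 be Hispanic attendance at routine sessions before and after the HKTP.

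- Change in the outcome as defined: H
- Change in total Hispanic attendance: (R1 + H) − R0
- Difference between the two: R0 − R1, the fall in routine attendance

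Illustration with assumed figures, since the document gives none: R0 = 20 per month and H = 12 per month. Let s of the 12 be patients who would otherwise have attended the routine sessions, with nothing else changing, so R1 = 20 − s.

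- s = 0: the outcome rises by 12; total attendance changes by (20 + 12) − 20 = 12.
- s = 6: the outcome rises by 12; total attendance changes by (14 + 12) − 20 = 6.
- s = 12: the outcome rises by 12; total attendance changes by (8 + 12) − 20 = 0.

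The defined outcome reads 12 in every case. It cannot tell these cases apart.

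**Outreach row**

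The label and first sentence count referrals by outreach staff. The second sentence lists five sources, of which outreach staff is one. Two readings are open:

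- Outreach referrals only. The value before the HKTP and at control centers depends on whether those centers had transplant outreach staff. The document does not say, so it may be anything from zero to a real positive count. New referrals cannot be separated from substituted ones.
- All referrals, recorded by source. This count exists in every cell and is comparable.

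Two abstractors could follow different readings.

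**Rows that do compare**

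Completed evaluations and waitlist additions (Table 2) do not refer to the HKTP and can be counted in every period, site and ethnic group.

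**The case against.** The strongest reply is that these rows are process measures. The Abstract groups outreach and session attendance under process and outcome measures, and the online surveys (Mixed methods research) already track HKTP attendance and the steps after outreach contact. None of H1 to H4 tests either count. Mapping components to outcomes needs counts close to each component, and HKTP attendance is a reasonable dose measure within the post period. All of this stands, and it limits the consequence. It does not remove the conflict: Table 2 separately labels the counts intermediate outcomes, and Aim 3 and Outcome measures put intermediate outcomes through a controlled pre-post evaluation.

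A second reply is that a condensed article leaves counting rules to the full protocol. That would answer a missing definition. Here the definition is printed, and it does not fit the comparison printed beside it.

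A reader might infer three stronger claims, none of which the document supports:

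- That the outreach row is also zero by definition before the HKTP and at controls. The row does not name the HKTP, and nothing says that any center lacked outreach staff.
- That the education count is zero by definition for non-Hispanic whites. The row says patients, without an ethnic limit; a count near zero follows from whom schedulers offer the clinic to.
- That the pathway conclusion would be wrong. If patients only switched clinics, completed evaluations and waitlist additions would stay flat unless the HKTP raised completion, so the discrepancy would be visible.

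**Conclusion.** The point holds in limited form. For the education row, three of the four period-by-site cells are zero by construction, and the controlled contrast equals the intervention-site post count. That follows from the definition and from control centers not running the HKTP; it needs no assumed figure. How far the count would overstate a gain in attendance depends on how many patients switch clinics, which is unknown. In the assumed example the overstatement runs from 0 to 12 out of 12.

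The outreach row has an ambiguity to resolve, not a degenerate comparison.

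The consequence is confined to the entry steps of the pathway analysis. Later steps remain comparable, and H1 to H4, including the transplant and waitlist hypotheses, do not use these counts.

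**What to change.** In Table 2:

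1. Define the education outcome as the number of patients attending any initial transplant education or evaluation session, HKTP or routine, reported by ethnicity, period and site.
2. Define the referral outcome as the number referred for evaluation from all sources, broken down by source, on the same basis.
3. Keep HKTP-session attendance and outreach referrals as fidelity or dose measures under Aim 2, alongside the online-survey metrics already planned.

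Monthly medical record review is already planned at intervention and control sites, so the change is mainly one of definition plus some extra abstraction. The main risk is data quality: routine-session attendance and referral source may be less completely recorded in pre-period and control-site charts. The document does not say how well either is captured, so availability should be checked before the definitions are fixed.

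### Donor evaluation time in Table 2 exists only for donors who finish a phase, so comparisons of it can reflect changed retention rather than changed speed

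*Protocol article*

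**What the plan says.** All of this is in the Protocol article, section Outcome measures and its Table 2.

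- The measure is labelled "Days for donor to complete each phase of evaluation" and defined as "The number of days from start to finish of each phase of living donor evaluation from initiation to clearance for donation to donation".
- The companion count is also limited to finishers: "The aggregate number of potential living donors who have completed each phase of the donor evaluation process".
- The other ways a work-up can stand or end appear in a separate row, which gives each donor's "evaluation status as: initiated, completed, ruled out, withdrew, alternate donor found". Nothing in the table ties that status to the time.
- Recipient waiting time, in the same table, is defined so that an unfinished wait still has a value: "The number of days patients have waited on the waiting list to date".
- On use: "Measures will be collected at intervention and control sites in pre and post periods". The stated purpose of the intermediate measures is to trace the pathways by which the programme may raise Hispanic LDKT rates.
- On the expected effect: "We expect that the pre-post change will demonstrate a higher number of potential donors who initiate evaluation and complete more steps".

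The section Statistical analysis plan adds that intermediate and final outcomes will be examined for association and that matched sites will be compared. The Discussion relies on mapping components to intermediate outcomes, and those to final outcomes, to learn which components work.

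**The concern.** A duration that needs a finish is conditional on finishing. Completing steps is the very thing the HKTP is meant to change, so the donors with a value before the programme and those with a value after it are selected differently. Suppose the programme keeps in work-up donors who would otherwise have left. The slower finishers then enter the average, and it lengthens although nobody is being evaluated more slowly.

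Control sites do not remove this, because the change in retention is expected where the HKTP runs. At stake is the pathway reading: a component that helps donors stay the course could be recorded as one that slows evaluation down. The point concerns the outcome as the table defines it, not an analysis model left unnamed.

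**Working it through.** **Inputs.** The article states no figure for donor evaluation time, exit rates or completion rates, so there is nothing of its own to reproduce here. Its one power statement concerns satisfaction scores and does not enter. All rates below are assumptions.

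**1. Retention changes, speed does not.** Let completion have constant rate h1 and all other exits constant rate h2, per month.

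- Mean time among finishers = 1/(h1 + h2).
- Share completing = h1/(h1 + h2).
- Before: h1 = 1/6, h2 = 1/3. Mean 1/(1/6 + 1/3) = 2.0 months; share (1/6)/(1/2) = 33%.
- After: h1 = 1/6, h2 = 1/6. Mean 1/(1/6 + 1/6) = 3.0 months; share (1/6)/(1/3) = 50%.

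The measure lengthens by 50% with h1 unchanged. Cumulative incidence of completion by time t is [h1/(h1 + h2)] × [1 − exp(−(h1 + h2)t)]. At 6 months this is 0.333 × (1 − e^−3) = 32% before and 0.5 × (1 − e^−2) = 43% after, so it moves the right way.

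**2. Speed improves and retention improves.** Mean completion time falls from 180 to 150 days, so the completion rate rises by 180/150 − 1 = 20%. The same formulas give:

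| Case | Mean completion time (days) | Mean time to other exit (days) | Mean among finishers (days) | Share completing |
|---|---|---|---|---|
| Before | 180 | 120 | 72 | 40% |
| After, exits unchanged | 150 | 120 | 67 | 44% |
| After | 150 | 180 | 82 | 55% |
| After | 150 | 240 | 92 | 62% |
| After | 150 | 360 | 106 | 71% |

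The sign is right if exits do not change and wrong in the three rows where they become less frequent.

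**3. Different distribution.** This is a simulation with lognormal completion times (log SD 0.6) and exponential exits. The median falls from 180 to 150 days and the mean time to exit rises from 120 to 360 days. Among finishers the mean goes from 136 to 151 days and the median from 121 to 130 days. The sign is wrong again, so the result does not depend on the exponential form.

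**4. Late cut-off, shown separately.** Assume no exits and entry uniform over 42 months (3.5 years × 12), cut at the end. Exponential times with true means of 3, 6, 9 and 12 months are then observed among finishers as 2.8, 5.0, 6.7 and 7.9 months (−8%, −17%, −26%, −34%). With the lognormal above (true mean 215 days), windows of 1, 2, 3.5 and 6 years give 143, 180, 197 and 205 days. Only a difference in follow-up between the groups compared would create a spurious contrast. The 6-year and 3.5-year periods in the article are for the UNOS data, and no window is given for the donor record review.

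**The case against.** The strongest reply is that a one-line table definition is not an analysis. Nothing says the days will be averaged over finishers, and start-to-finish time is also the raw material for a censored or competing-risk analysis that an unseen analysis plan may contain. The table also collects each donor's status and the number finishing each phase. A reader who saw 33% become 50% beside 2.0 becoming 3.0 months would not conclude simply that the process had slowed.

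Part of this stands. The data needed are largely planned, and reporting the rows side by side softens the misreading. It does not remove the problem: the measure itself has no value for an unfinished phase, and any comparison of it as defined carries the selection.

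Two stronger readings are tempting, and the article does not support them.

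- **That late cut-off alone would make the post period look faster under no effect.** The article gives neither the record-review windows nor any rule on following pre-period donors into the post period. A cut-off shared with control sites would largely cancel in the controlled contrast if durations and entry patterns are similar.
- **That donors who leave are lost altogether.** The loss is per phase: someone who withdraws late still contributes every phase already finished.

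**Conclusion.** The point holds for the measure as Table 2 defines it. It can respond to retention as well as speed, and it can move in the wrong direction: +50% among finishers with unchanged speed in the first example, and 72 days rising to between 82 and 106 days despite a true improvement in the second. A wrong sign is possible, not certain; it needs exits or follow-up to differ between the groups compared, and with exits unchanged the sign is right (72 to 67 days).

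The direction follows from the definition together with the stated expectation that more steps will be completed. The sizes rest on assumed rates. The cut-off figures are illustrative only.

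A reader might also infer that the main results are at risk. They are not: this is one intermediate outcome, it is not part of H1 to H4, and the stated power does not depend on it. It should be corrected because the pathway interpretation leans on such measures.

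**What to change.** For each phase, take all donors who start it and report the cumulative incidence of completion at fixed times, for example 3, 6 and 12 months. Treat ruled out, withdrew and alternate donor found as competing exits, each with its date, and censor work-ups still open. Define pre and post cohorts by start date and give them the same length of follow-up at all four sites. Keep days among finishers as a descriptive figure, shown with the share finishing.

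Cumulative incidence rises with either better retention or faster completion. If speed alone is the question, add the completion rate among donors still in the phase.

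The cost is small: a disposition date in a record review already planned for each potential donor, and a little more analysis. With equal follow-up, the latest starters will contribute less.

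Suggested wording for Table 2: *Cumulative proportion of donors starting each phase who complete it by 3, 6 and 12 months, with other dispositions as competing events and open evaluations censored; days among completers reported descriptively.*
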